## Institutional Review Board (IRB)

Department of Physiotherapy & Rehabilitation

Jashore University of Science & Technology

mail: [[contact]](mailto:[contact]) website: <https://ptr.just.edu.bd/>

Kruskal–Wallis tests for non-normally distributed data. Primary intervention effects across three assessment points (T1, T2, T3) will be evaluated using linear mixed-effects models (LMMs), with group specified as the between-subjects factor and time as the within-subjects factor, and pre-specified baseline covariates (age, sex, and body mass index). All covariates were measured at baseline prior to randomization and were included based on their known associations with executive function; post-randomization or time-varying covariates were not adjusted for to avoid mediation or over-adjustment bias. Although sample size estimation was based on mixed-model ANOVA, LMMs were selected for primary analysis due to their robustness to missing data and flexibility in modelling repeated measures. Model assumptions, including normality and homoscedasticity, will be assessed, and robust or rank-based alternatives will be applied if violations are detected. Significant group  $\times$  time interactions will be explored using simple main effects with Holm–Bonferroni correction for multiple comparisons. Effect sizes will be reported as partial  $\eta^2$  for mixed models and Cohen’s  $d$  (pooled SD) for pairwise comparisons, interpreted using conventional benchmarks. Within-group changes across time points will be examined using paired-samples  $t$ -tests, interpreted in relation to both statistical significance ( $p < 0.05$ ) and established minimal clinically important differences (MCID) where available. To control family-wise error across multiple primary outcomes, Holm–Bonferroni adjustment will be applied. Missing data will be handled under the assumption of missing at random (MAR) using an intention-to-treat approach with multiple imputation. Sensitivity analyses will be performed to explore the potential impact of outcome-dependent exclusions, such as participants with fewer than 50% correct responses on Go trials. Multivariate relationships among primary outcomes will be further examined using multivariate analysis of covariance (MANCOVA), adjusting for baseline covariates and assessing assumptions of multivariate normality and homogeneity of covariance matrices. This analytical strategy ensures robust, unbiased, and clinically interpretable inference in longitudinal, multigroup studies.

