| Intervention details | All participants will receive a healthy-lifestyle guideline booklet to follow throughout the 24-week study. The wait-list control group will receive these guidelines plus biweekly discussion sessions during their initial 12-week period and will later receive the same intervention as the experimental group. The experimental group will complete a 12-week, five-component multimodal program delivered by trained physiotherapists, with                                                                                                                                                                                                                                                                                                                                                                                                                     |

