|                              | all procedures, dosages, and progressions monitored by four research assistants for consistency. Each 60-minute session, conducted five times per week in small groups, will include yoga (10 minutes), aerobic exercise (15 minutes), strengthening exercises (10 minutes), neurocognitive tasks (15 minutes), and music-based mindfulness (10 minutes), with structured rest intervals and progressive adjustments based on individual abilities. Detailed intervention content is presented in a supplementary file. A follow-up assessment will occur 12 weeks after the intervention to evaluate sustained effects, during which all participants will continue following lifestyle guidelines, and the control group will undergo the experimental intervention, accompanied by two discussion sessions addressing the health needs of children with ASD. |
| Intervention provider | Experienced and qualified health professionals                                                                                                                                                                                                                                                                                                                                                                                                                                                                                                                                                                                                                                                                                                                                                                                                                  |

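### The three-time-point group × time test does not isolate the randomised 12-week effect, and T3 cannot show sustained effects between arms, because the wait-list arm is treated between T2 and T3

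*Protocol*

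**What the plan says.** All references are to the protocol, Annexure B – Research Methodology.

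**Intervention details row.** The study lasts 24 weeks: "All participants will receive a healthy-lifestyle guideline booklet to follow throughout the 24-week study". For the control arm: "The wait-list control group will receive these guidelines plus biweekly discussion sessions during their initial 12-week period and will later receive the same intervention". On the last assessment: "A follow-up assessment will occur 12 weeks after the intervention to evaluate sustained effects". During that same follow-up window, "the control group will undergo the experimental intervention".

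**Statistical analysis row.** The primary analysis is given as "Primary intervention effects across three assessment points (T1, T2, T3) will be evaluated using linear mixed-effects models (LMMs". The structure of that model is then described in these terms: "with group specified as the between-subjects factor and time as the within-subjects factor". Where the interaction of the two factors proves significant, the plan says that such "time interactions will be explored using simple main effects with Holm–Bonferroni correction for multiple comparisons". Partial η² is to be reported for the mixed models. Paired t-tests are planned for within-group change, and Holm–Bonferroni is to be applied across the primary outcomes. No time point or contrast is named as the primary one.

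**The concern.** T1, T2 and T3 are read here as baseline, week 12 and week 24, which is what a 12-week programme, a follow-up 12 weeks later and a 24-week study imply.

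The randomised arms differ in access to the programme only between T1 and T2. By T3 both have had it: the experimental arm has been off it for 12 weeks, and the wait-list arm has just finished. The plan nevertheless places T3 inside the primary evaluation on the same footing as T2, and gives the follow-up the task of showing sustained effects.

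Two things are at stake. A significant interaction, or a large partial η², may be reported as the effect of the 12-week programme when part or all of it comes from T3. And a benefit that lasts perfectly would appear at T3 as no difference between arms, while a partly retained benefit would appear as an advantage for the wait-list arm.

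**Working it through.** The document gives no sample size, effect size, power or correlation, so there is no figure of the plan's own to reproduce. Everything below rests on assumptions and serves only to show direction and rough size.

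**Assumptions.** Effect d = 0.5 SD at T2. The wait-list arm gains the same d by T3. The experimental arm keeps a share s of its effect at T3. SD is equal at all visits, with the same correlation ρ between any two visits; n per arm; two-sided α = 0.05; two randomised arms only.

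**1. What T3 estimates.** Relative to no programme, the experimental arm stands at s·d and the wait-list arm at d, so the expected T3 difference is s·d − d = (s − 1)d. A control arm that never had the programme would give s·d.

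| Share kept, s | T3 difference, wait-list treated | T3 difference, control never treated |
|---|---|---|
| 1.00 | 0 | +0.50 |
| 0.75 | −0.125 | +0.375 |
| 0.60 | −0.20 | +0.30 |
| 0.50 | −0.25 | +0.25 |
| 0 | −0.50 | 0 |

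**2. Chance that T3, read alone, significantly favours the wait-list arm.** Take s = 0.60 and ρ = 0.7. The SD of the T1-to-T3 change is √(2 × 0.3) = 0.775, and the non-centrality is −0.2 / (0.775 × √(2/n)).
- n = 20: −0.82, probability 0.122
- n = 30: −1.00, probability 0.164
- n = 60: −1.41, probability 0.289

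**3. What the interaction responds to.** With arm differences a at T2 and b at T3, the 2-df group × time test has non-centrality λ = n(a² − ab + b²) / (3(1 − ρ)). For n = 40 and ρ = 0.5 this is 26.67 × (a² − ab + b²).

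| Scenario | a | b | λ | Rejection rate |
|---|---|---|---|---|
| No effect in either period | 0 | 0 | 0 | 0.05 |
| Effect fully kept | 0.5 | 0 | 6.67 | 0.63 |
| 75% kept | 0.5 | −0.125 | 8.75 | 0.76 |
| 50% kept | 0.5 | −0.25 | 11.67 | 0.87 |
| Wholly lost | 0.5 | −0.5 | 20.00 | 0.985 |
| No T2 difference, wait-list 0.5 SD ahead at T3 | 0 | −0.5 | 6.67 | 0.63 |

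The T1-to-T2 contrast alone has power 0.61 in the same setting. The omnibus test becomes more significant as durability gets worse. It also rejects as often with no T2 difference and a T3 gain in the wait-list arm as it does with a fully retained T2 effect.

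**4. Cost of using the interaction as a gate.** Probability that T2 significantly favours the experimental arm, tested directly and then only after a significant interaction (simulation, normal approximation, no Holm adjustment):
- s = 1, n = 20, ρ = 0.5: 0.35 → 0.27
- s = 1, n = 40, ρ = 0.5: 0.61 → 0.54
- s = 1, n = 60, ρ = 0.7: 0.94 → 0.93
- s = 0.6, n = 40, ρ = 0.7: 0.82 → 0.82

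The loss is about 0 to 8 percentage points.

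**5. If healthy children are a third level of group.** The text leaves this open. If the programme does nothing, but healthy children change by 0.3 SD more than the ASD arms at both T2 and T3, the 4-df interaction rejects in 26% (ρ = 0.5) to 42% (ρ = 0.7) of trials at n = 40 per group.

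**The case against.** A reader might infer that the primary test is not a test of the intervention at all. For the two randomised arms that goes too far. If the programme does nothing in either period, the interaction keeps its 5% level. If it works, the interaction responds through T2, with power no lower than that of the T2 contrast in the cases computed. The T2 simple effect remains a clean randomised comparison, and gating it costs little. The stronger reading would become fair only if healthy children are a level of the group factor, which the document does not say.

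A reader might also infer that the effect is diluted by averaging over T2 and T3. That would describe a time-averaged group main effect, and the plan names no such test.

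It can further be said that exact contrasts are often left to a statistical analysis plan, that the protocol never states that sustained effects will be judged by the T3 arm difference, and that the planned paired tests already cover within-arm change. These points are fair as far as they go. But the protocol does fix the primary evaluation over all three visits, describes simple effects only as follow-up to a significant interaction, and assigns T3 to sustained effects without acknowledging that the comparator has by then been treated. That is a stated analysis aimed at the wrong contrast rather than a missing detail.

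**Conclusion.** The point stands in this form: the three-visit interaction is valid against no effect at all in the two randomised arms, but neither its significance nor its partial η² isolates the randomised 12-week effect, and the T3 arm difference cannot show sustained effects against control.

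The second conclusion follows from the design. Under equal response in both arms the expected T3 difference is (s − 1)d, so for any positive effect d it is zero at full retention and negative at anything less. The rejection rates (0.63 rising to 0.985), the 12% to 29% chance of T3 favouring the wait-list arm, and the gating cost of 0 to 8 points all depend on assumed effect, retention, correlation and sample size. They are not predictions for this trial. The main harm is to interpretation of the primary result and of the durability claim; the loss of power is modest.

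**What to change.** In the Statistical analysis row:

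- Name the experimental minus wait-list difference in T1-to-T2 change, in the two randomised ASD arms only, as the primary effect. Test it directly, without the three-visit interaction as gatekeeper.
- Apply the planned Holm–Bonferroni adjustment across the primary outcomes to those T2 contrasts.
- For T3, report with confidence intervals the T2-to-T3 change in the experimental arm, as uncontrolled maintenance, and the T2-to-T3 change in the wait-list arm, as a within-arm replication.
- State that the T3 difference between arms will not be read as a treatment effect or as a sustained effect, and align the follow-up sentence in the Intervention details row with this.

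The cost is wording only: visits, measures and data collection stay as they are. The downside is that the maintenance claim becomes explicitly uncontrolled. The change should be made before outcome data are seen, since choosing T2 afterwards would be post hoc.

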| Research Title       | Effectiveness of a Five-Component Multimodal Intervention on Executive Function in Children with Autism Spectrum Disorder: A Randomized Controlled Trial                                                                                                                                                                                                                                                                                                                                                                                                                                                                                                                                                                                                                                                                                                              |
| Eligibility criteria | Qualified health professionals will recruit participants through an impartial screening process that adheres to predefined inclusion and exclusion criteria. Children aged 4–18 years of both sexes with a confirmed ASD diagnosis according to DSM-5 and CARS-2, assessed by a child psychiatrist, and who consent to participate in a 12-week intervention will be included. Participants will be excluded if they have cerebral palsy, Down syndrome, ADHD, or any recent (past six months) muscle injury, sprain, head injury, skin laceration, or other conditions that may hinder exercise or study outcomes. Children in the healthy control group will undergo the same interview to confirm typical development and will complete the same outcome measures to compare whether the ASD group can achieve normal developmental levels after the intervention. |

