| Outcome measurement   | 
Primary outcomes
 
The primary outcome will be Executive Function, assessed through three subcomponents: Inhibitory Control, Cognitive Flexibility and Working Memory. Inhibitory Control (IC) will be measured using the Go/No-Go (GNG) task; Cognitive Flexibility will be assessed with the Trail Making Test (TMT); Working Memory (WM) will be evaluated using the Corsi Block Tapping Task (CBTT), Forward Digit Span (FDS) test, and Backward Digit Span (BDS) test.
 
Secondary outcomes
 
The secondary outcomes will be social responsiveness and autism-related behavioral changes. Social responsiveness will be assessed using the Social Responsiveness Scale, Second Edition (SRS-2), and ASD-related characteristics will be evaluated using the Autism Treatment Evaluation Checklist (ATEC)
               |
| Statistical analysis  | Statistical analysis will be conducted using SPSS version 26. Continuous variables will be summarized as mean $\pm$ standard deviation (SD), and categorical variables as frequencies and percentages. Baseline differences across the three groups (two ASD intervention groups and healthy controls) will be examined using one-way ANOVA for normally distributed variables and                                                                                                                                                                                                                                                                                                                                                                                                                                                                              |

IRB of the Department of Physiotherapy and Rehabilitation established on March 27, 2024 and was approved by the departmental academic committee meeting resolution.

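### The primary mixed model does not limit its group factor to the two randomised ASD arms, so a significant group × time test is not by itself evidence that the intervention works

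*Protocol*

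**What the plan says.** All references are to the Protocol, Annexure B (Research Methodology).

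- **Role of the healthy children (Eligibility criteria).** They are selected by interview and not randomised, and they "will complete the same outcome measures to compare whether the ASD group can achieve normal developmental levels after the intervention". That is a benchmark purpose. No visit schedule is given for them.
- **Groups (Statistical analysis).** The section spells out its groups once, for the baseline comparison: "Baseline differences across the three groups (two ASD intervention groups and healthy controls".
- **Primary model.** The next sentence hands the test of the intervention over T1, T2 and T3 to a mixed model. Its factors are set out in these words: "with group specified as the between-subjects factor and time as the within-subjects factor". The levels of the group factor are not listed.
- **Follow-up.** Significant group × time "interactions will be explored using simple main effects with Holm–Bonferroni correction for multiple comparisons". Partial η² is the effect size for the mixed models. No experimental versus wait-list contrast is named as the primary test.
- **Closing description.** "This analytical strategy ensures robust, unbiased, and clinically interpretable inference in longitudinal, multigroup studies".

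**The concern.** The only group definition in the section has three levels, and the model sentence that follows uses the same word without narrowing it. A programmer following the text would reasonably fit a model with three groups and three time points.

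The interaction test then has 4 degrees of freedom. Its null hypothesis says that all three groups change in parallel, which includes healthy and autistic children changing equally. Randomisation says nothing about that part. Typically developing children may gain more or less than children with ASD from repeating cognitive tasks or from maturation. If so, the null is false even when the intervention does nothing.

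Two things are at stake. The first is interpretation: the interaction and its partial η² sit under the label of primary intervention effects but are not specific to the intervention. The second is the standard error: if one residual variance is shared by all three groups and the healthy children are less variable, the standard error of the randomised contrast comes out too small.

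**Working it through.** The document gives no sample size, SD, correlation or effect size, so there is no figure of its own to reproduce. The inputs below are assumptions, shown as ranges.

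**Inputs**
- From the protocol: three groups, three time points, and 0.05 as the significance level (stated for the paired tests, taken here for the interaction).
- Assumed: *n* = 20, 30 or 60 per group, equal sizes; ASD SD = 1; compound symmetry with correlation ρ = 0.7; both ASD arms flat, so no treatment effect; healthy children gain an extra *g* = 0.2 or 0.3 SD at T2 and T3.

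**1. Rejection rate of the omnibus interaction**

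The mean changes are (0,0,0), (0,0,0) and (0,*g*,*g*). After removing group and time means, the squared interaction effects sum to (2/3) × (2*g*²/3) = 4*g*²/9.

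Non-centrality: λ = *n* × (4*g*²/9) / (1 − ρ). Degrees of freedom: (3−1)(3−1) = 4 and 3(*n*−1)(3−1) = 6(*n*−1).

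For *n* = 30 and *g* = 0.2: λ = 30 × (4 × 0.04/9) / 0.3 = 1.78 on 4 and 174 df.

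| *n* per group | df | λ (*g* = 0.2 / 0.3) | Omnibus significant (*g* = 0.2 / 0.3) |
|---|---|---|---|
| 20 | 4, 114 | 1.19 / 2.67 | 11.4% / 21.2% |
| 30 | 4, 174 | 1.78 / 4.00 | 15.3% / 31.2% |
| 60 | 4, 354 | 3.56 / 8.00 | 28.3% / 59.8% |

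At ρ = 0.5 and *n* = 30 the rates are 10.8% / 19.5%. With *g* = 0, where healthy children differ in level but change in parallel, the rate is 5.0%. The same test on the two randomised arms alone is 5.0% in every scenario (5.1% by simulation at *n* = 30, ρ = 0.5).

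**2. What survives the planned follow-up tests**

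The sequence was simulated: omnibus test first, then Holm over the three group pairs at each time. It assumes no treatment effect, ρ = 0.7 and a healthy level 1 SD away from the ASD level. False experimental versus wait-list findings at T2:

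- Equal SDs: 0.8–1.4% (*n* = 20), 1.0–1.7% (*n* = 30), 1.6–3.6% (*n* = 60).
- Healthy SD half the ASD SD: 1.1–7.6%, above 5% only at *n* = 60 with *g* = 0.3.

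**3. Shared residual variance**

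With healthy SD equal to *s* times the ASD SD and equal group sizes, the pooled variance is (1 + 1 + *s*²)/3. The standard error of the ASD contrast is then multiplied by its square root, and the two-sided error of an unadjusted contrast is 2 × [1 − Φ(1.96 × ratio)].

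- *s* = 0.5: variance 0.75, ratio 0.866 (13% too small), error 9.0%.
- *s* = 0.7: variance 0.83, ratio 0.911 (9% too small), error 7.4%.

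**The case against.** The case for leaving the text alone has real substance.

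- **The levels of the group factor are never listed.** The three-group phrase belongs to the baseline comparison. The model sentence speaks of intervention effects, its covariates are described as measured before randomisation, and the analysis is by intention to treat. Those terms suit randomised children only. A reader might infer that the healthy children definitely are a third level of the model. The text permits that reading, and the closing multigroup description favours it, but nothing establishes it. What stands is that the protocol does not restrict the factor.
- **The schedule is unknown.** If healthy children are measured only once, the three-by-three interaction cannot arise.
- **The omnibus rate is not the error rate of a treatment claim.** A reader might infer from the table that up to 60% of null trials would falsely declare the intervention effective. They would not. In that scenario the omnibus null really is false, and the planned Holm-corrected comparisons stand between it and a claim about the arms. Step 2 shows how much they hold back. Counting T2 or T3 without adjustment across times, the maxima were 6.1% (equal SDs) and 11.7% (half SD).
- **Unequal variance is anticipated.** The plan checks homoscedasticity and promises robust or rank-based alternatives. The 7–9% error arises only if a common variance is kept despite that check.
- **Detail may sit in a statistical analysis plan.** That would excuse silence, but here the protocol itself fixes the factor and the test that opens the follow-up comparisons, and leaves both open to a non-specific reading.

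**Conclusion.** The point holds in a limited form. As written, the primary model is not confined to the randomised arms. If the healthy children enter it at T1–T3, a significant group × time interaction, and the partial η² reported with it, cannot by themselves be read as a treatment effect.

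Under the assumed inputs the omnibus test opens the follow-up comparisons in 11–60% of trials with no treatment effect, instead of 5%. The sizes depend on *n*, ρ and *g*, none of which the document supplies. The mechanism requires healthy children to change differently over time; a constant difference in level causes no inflation.

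The effect on false experimental versus wait-list findings at T2 is much smaller: about 1–4% with equal SDs, and about 1–7.5% if healthy children have half the ASD SD. The variance problem is conditional on the planned check failing or being ignored.

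This should be fixed, with moderate confidence. It is an ambiguity with a clear consequence on one natural reading, not a demonstrated invalid analysis.

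**What to change.** In the Statistical analysis row of Annexure B:

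1. State that the primary mixed model is fitted to the two randomised ASD arms only, with variance estimated from those arms.
2. Name the experimental versus wait-list contrast from that model as the test of the intervention effect, and attach the reported effect size to it.
3. Move the healthy children to a separate comparison, labelled as a non-randomised benchmark, that answers the question in the eligibility section. State at which assessments they are measured.

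The cost is a few sentences. No participants, visits or data are lost, and the healthy children still serve their stated purpose. The planned baseline comparison across three groups is a separate matter and need not change for this point.

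### The primary mixed model leaves the child's own T1 score out of its covariates, and age, sex and BMI cancel from the T2 group × time contrast: precision is lost, without bias

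*Protocol*

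**What the plan says.** All of this stands in the Statistical analysis row of Annexure B, which runs on under the next page header.

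- Model: "Primary intervention effects across three assessment points (T1, T2, T3) will be evaluated using linear mixed-effects models (LMMs".
- Factors in that model, group between children and time within: the row names no others.
- Covariates: "pre-specified baseline covariates (age, sex, and body mass index". They are chosen for their association with executive function. The T1 value of the outcome is not among them.
- Covariates that change after randomisation are excluded: "post-randomization or time-varying covariates were not adjusted for to avoid mediation or over-adjustment bias".
- Route to the group comparison: a significant group × "time interactions will be explored using simple main effects", with Holm–Bonferroni correction.
- Sample size: "Although sample size estimation was based on mixed-model ANOVA". No number of children, effect size, power or correlation is given.

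The Eligibility criteria row of the same annexure sets a wide age range: "Children aged 4–18 years of both sexes with a confirmed ASD diagnosis". The Intervention details rows state that the wait-list arm receives the programme during the follow-up period. The comparison of treated with not-yet-treated children therefore rests on the change from T1 to T2.

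**The concern.** When T1 is one of the outcomes and each arm has its own T1 mean, the T2 interaction compares the arms on the change from T1 to T2. A covariate that is fixed over time and entered as a main effect raises or lowers a child's level by the same amount at every visit, so it disappears when T1 is subtracted from T2. The adjustment that the plan justifies by its link to executive function then adds nothing to the test that opens the way to all further comparisons.

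The T1 score is likely to be among the best predictors of the T2 score, and it is used only by subtraction. Subtraction over-corrects whenever the T1–T2 correlation is below 1. What is at stake is power for several primary tests that share a Holm–Bonferroni correction, and avoidable sensitivity to a chance T1 difference between the randomised arms.

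**Working it through.** **Inputs.** The model, factors and covariates are those in the Statistical analysis row. The protocol gives no standard deviation, ρ, effect size or sample size, so there is no stated figure to reproduce. Assumed here: equal standard deviation σ at T1 and T2, and ρ from 0.3 to 0.9. The sample-size illustration also assumes a difference of 0.5 SD, two-sided alpha 0.05 and 80% power. Both σ and ρ are taken after adjusting for age, sex and BMI.

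**Step 1: cancellation.** For a child in arm g (0 or 1) with baseline covariates x:

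- E(Y1) = μ1 + β1·g + γx
- E(Y2) = μ2 + β2·g + γx
- E(Y2 − Y1) = (μ2 − μ1) + (β2 − β1)·g

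The term γx is gone. The interaction is β2 − β1. Because β1 is free, the T1 levels carry no further information about it.

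**Step 2: check by simulation.** 60 simulated trials, 40 children per arm, three visits, ages uniform over 4–18, random-intercept model. The child-level residual SD was 0.7 and the visit error SD 0.6, so ρ given the covariates is 0.49/(0.49 + 0.36) = 0.58. Mean standard error of the T2 effect:

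| Model | Complete data | 15% of post-baseline values missing |
|---|---|---|
| Group × time, no covariates | 0.1879 | 0.2020 |
| Same, plus age, sex, BMI | 0.1879 | 0.2015 |
| Common T1 mean for both arms, plus age, sex, BMI | 0.1678 | 0.1827 |
| Group × time, plus covariate × time terms | 0.1919 | 0.2047 |

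With complete data the covariates moved the estimate by at most 1e-14. With missing data they moved it by at most 0.034 in any one trial and left the standard error almost unchanged. The common T1 mean gave a variance ratio of (0.1678/0.1879)² = 0.80, against (1 + 0.58)/2 = 0.79 from the formula in Step 3. Covariate × time terms gave no gain, as expected, because the simulated data contained no such interaction.

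**Step 3: size of the loss.** Per-child variances:

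- Planned change contrast: 2σ²(1 − ρ)
- Adjusted for T1: σ²(1 − ρ²)
- Ratio, adjusted to planned: (1 − ρ²)/[2(1 − ρ)] = (1 + ρ)/2

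**Step 4: the same in children per arm**, under the assumed 0.5 SD difference. The last column is the power of the planned contrast at the size that gives the adjusted analysis 80%.

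| ρ | (1+ρ)/2 | Variance saved | n per arm, planned | n per arm, adjusted | Power of planned contrast |
|---|---|---|---|---|---|
| 0.3 | 0.65 | 35% | 88 | 58 | 62% |
| 0.5 | 0.75 | 25% | 63 | 48 | 69% |
| 0.7 | 0.85 | 15% | 38 | 33 | 75% |
| 0.8 | 0.90 | 10% | 26 | 23 | 76.5% |
| 0.9 | 0.95 | 5% | 13 | 12 | 78% |

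**Step 5: chance imbalance.** If the arms differ at T1 by δ, the change-score estimate is shifted by (1 − ρ)δ in the opposite direction. At ρ = 0.7 and δ = 0.2 SD this is 0.3 × 0.2 = 0.06 SD. Adjustment for T1 removes it. Averaged over randomisations the shift is zero.

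**The case against.** The strongest reply is that the planned model is valid and standard. Under randomisation its contrast is unbiased, and the shift in Step 5 is conditional on one imbalance. That stands. A reader might infer that the primary analysis is wrong or biased, and the protocol does not support that.

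Second, the parameterisation is inferred. The protocol does not define T1 in words. It does not say that arm means at T1 are free or that covariates enter only as main effects. Excluding time-varying covariates does not by itself exclude interactions of baseline covariates with time. An analysis plan could settle these details. This lowers certainty, but the protocol does fix a covariate list, calls it pre-specified, and leaves the T1 score off it.

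Third, a reader might infer that age, sex and BMI are useless throughout. They are not: the cancellation concerns the interaction contrast. In the simple main effect of group at T2 they do add precision. That comparison still makes no use of the child's T1 score, and it is reached only after a significant interaction.

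Fourth, the gain depends on a correlation that nobody has stated, and at ρ of 0.8 to 0.9 it is small. A wide age range makes it plausible that much of the crude T1–T2 correlation is due to age. The adjusted ρ would then be lower and the gain larger. How much variance age explains is still an assumption.

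Last, a reader might want BMI replaced by a CARS-2 severity score. The protocol mentions CARS-2 only for eligibility ("confirmed ASD diagnosis according to DSM-5 and CARS-2, assessed by a child psychiatrist"). Neither the outcome list nor the questionnaire in Annexure E names it as a recorded measure, and nothing shows that it would predict better than BMI once T1 is in the model. That change is not proposed.

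**Conclusion.** The point holds as an improvement in precision, not as the correction of an error. On the natural reading, the listed covariates contribute nothing to the T2 group × time contrast with complete data and almost nothing with missing data. Adjusting for the T1 score would cut the variance of that contrast by between 35% (ρ = 0.3) and 5% (ρ = 0.9).

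The cancellation rests on T1 being the baseline visit, free arm means at T1 and covariates as main effects. The size rests on equal standard deviations at T1 and T2 and on the assumed ρ. The variance ratio does not depend on the assumed 0.5 SD difference or on alpha; the numbers of children and the power figures do.

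**What to change.** For the comparison of the two randomised ASD arms, state one of the following for each primary test:

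- Model T2 and T3 as outcomes, with the T1 score of the same test as a covariate by visit, and keep age, sex and BMI.
- Keep T1 as an outcome and constrain the two randomised arms to one T1 mean, with age, sex and BMI retained. With the constraint in place, these covariates can contribute even as main effects.

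Do not extend the constraint to the healthy controls. They are not randomised and are expected to differ at T1, so their comparison stays a separate analysis. Define T1 in words at the same time. Covariate × time terms and a spline for age are optional.

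The cost is small: a separate two-arm model or a partial constraint, and revised wording. The T1 scores are already part of the planned assessments. The change should be made before any unblinded analysis.
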